### Control Group

Mothers in the control group will receive only the standard iron supplement. Although iron itself may influence oxidative stress, this effect can be controlled by equalizing iron intake across groups. They will be counseled on dietary sources of antioxidants and offered *M. oleifera* supplementation after study completion if desired. This delayed intervention strategy has been approved by the local ethics committee and was explained during informed consent.

To minimize the risk of measurement and performance bias, participants in the control group were not informed about the specific intervention given to the other group.

### Biomarker Analysis

#### Heavy Metal Analysis

The measurement was conducted to determine Hg, Pb, and Cd levels in the blood of pregnant women during the second or third trimester. Heavy metals were analyzed using inductively coupled plasma mass spectrometry (ICP-MS) (Thermo Fisher Scientific, Bremen, Germany) and performed in micrograms per liter. To ensure analytical accuracy and method validation, we used certified reference materials (CRM BCR®-636, lyophilized human blood, Joint Research Center-JRC, European Commission) as a quality control standard. For quality assurance and quality control (QA/QC), calibration curves were generated using multielement standard solutions of known concentrations. Blank samples were included in each analytical batch to monitor contamination.

#### Oxidative Stress Analysis

In this study, 8 OHdG and MDA are used as biomarkers of oxidative stress because they capture two complementary pathways: DNA oxidative damage and lipid peroxidation, respectively. Both markers have been validated in pregnant populations exposed to heavy metals such as Pb, Cd, and Hg. Alternative enzymatic antioxidants (eg, glutathione peroxidase, catalase) require immediate enzyme activity preservation, which cannot be guaranteed under our field conditions; 8 OHdG and MDA, by contrast, remain stable in frozen plasma and are therefore better suited to the study’s logistics.

Plasma concentrations of MDA (nmol mL⁻¹) will be quantified in duplicate using a commercially available ELISA kit (Thermo Fisher Scientific, Bremen, Germany). 8 OHdG (ng mL⁻¹) will be measured in duplicate with a validated ELISA kit (Bioassay Technology Lab, Shanghai Korain Biotech Co. Ltd). For each assay run, an 8-point standard curve, reagent blanks, and low-/high-quality control samples will be included. Concentrations will be derived from the standard curves using a 4-parameter logistic model, and any sample with a coefficient of variation > 10 % on duplicate readings will be reassayed. Laboratory technicians will be blinded to group allocation to minimize measurement bias.

### Data Analysis

All analyses will be conducted using the R statistical software (latest version). Data entry and cleaning will be conducted by trained staff using a double-entry verification. For 24-hour food recall data, participants will be asked to estimate portion sizes using visual aids, and data will be reviewed during collection for completeness and clarity. For the FFQ, if participants leave implausible answers (eg, extremely high frequency), the data will be reviewed and clarified during the interview or excluded from analysis after documentation. Implausible intake frequency will be cross-checked with interview notes and food recall summaries to determine plausibility. An intention-to-treat (ITT) analysis will be performed to preserve the benefits of initial group allocation. For missing or partial responses, multiple imputation will be considered for covariates in the adjusted models. For missing outcome data at follow-up, last observation carried forward (LOCF) will be used when feasible. Sensitivity analyses will be conducted to assess the robustness of findings under different missing data assumptions. Outliers will not be automatically excluded unless clear reporting errors are confirmed. Outliers in biomarker measurement will be identified using the interquartile range method and retained unless proven to result from analytic error or sample contamination. All statistical analyses will be conducted with and without outliers to assess the robustness of the results.

Descriptive statistics will summarize participant characteristics. All continuous variables, including heavy metal concentrations and biomarker levels, will be checked for normality before analysis. In the case of non-normal distributions, appropriate data transformations (eg, log transformation) will be applied. If normality cannot be achieved, nonparametric tests (eg, Mann–Whitney *U* or Wilcoxon signed-rank test) will be used as alternatives. Analysis of group differences (pre- and postintervention). For each group, analysis will be conducted using the paired *t* test or Wilcoxon signed-rank test, depending on data distribution, to assess changes in heavy metals, MDA, and 8-OHdG levels before and after intervention. The significance level (alpha) will be set at .05, and all tests will be one-tailed.

For comparison between the groups (intervention vs control), analysis will be conducted using the difference-in-differences (DiD) method to measure the difference in changes between the intervention and control groups. The results will provide an overview of the impact of moringa leaf supplementation on the reduction of heavy metal levels and prevention of DNA damage in pregnant women. To address potential selection bias and confounding due to the nonrandomized design, we will use analysis of covariance (ANCOVA) to adjust for baseline differences in key variables such as maternal age, gestational age, education level, and baseline levels of heavy metals, MDA, and 8-OHdG.

Assumptions for ANCOVA will be checked using diagnostic plots and tests. Normality of residuals will be checked using the Shapiro–Wilk test and Q-Q plots. The homogeneity of variance test will use the Levene test from the car package. Linearity and homoscedasticity will be checked using residual versus fitted plots.

The interaction effects between intervention status and baseline heavy metal levels will be examined by adding interaction terms to the ANCOVA models. Additionally, stratification will be considered a sensitivity analysis to minimize bias. Baseline heavy metal levels will be included as covariates in the statistical models to account for variation in environmental exposure across recruitment areas. In addition, we will conduct exploratory subgroup analyses to assess potential effect modifiers. Outcomes will be examined separately for each heavy metal to assess whether the reduction effect of *M. oleifera* differs by metal type. Additional exploratory subgroup analyses may include stratification by trimester of pregnancy, nutritional status (BMI), and geographic location/pollution source.

If substantial differences are observed, these findings will be interpreted cautiously due to limited statistical power. All subgroup analyses will be considered hypothesis generating and reported transparently. If no significant interaction is found, primary analyses will focus on aggregate outcomes across all participants. Reduction in each individual heavy metal will be reported separately, along with a composite index. No interim analyses or stopping rules are planned due to the short duration of the trial and the nature of the design.

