**Methods:**

A quasi-experimental, nonrandomized pre-post test design is used. Pregnant women with elevated heavy metal levels, identified through initial screening, will be included in the intervention group, receiving *M. oleifera* supplementation for 2 months. The control group will consist of women from similar geographical regions who will not receive the intervention. Primary outcomes will include changes in heavy metal concentrations, measured using inductively coupled plasma mass spectrometry (ICP-MS). Secondary outcomes will focus on reductions in oxidative stress biomarkers, measured via enzyme-linked immunosorbent assay (ELISA). Statistical analyses, including analysis of covariance (ANCOVA), will be used to adjust for baseline differences between the groups.

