The required sample size was calculated using an estimated effect size (Cohen *d*) of 0.42, derived from a previous intervention study in South Sulawesi, which assessed the effects of *M. oleifera* supplementation on oxidative stress biomarkers in pregnant women exposed to passive smoking [37]. The study reported a mean difference in 8-OHdG levels between treatment groups of approximately 12.96 ng/mL with a pooled SD of ~30.68 ng/mL, yielding a moderate effect size. Using a 1-sided test with *α*=.05 and 80% power, the minimum required sample size is 37 participants per group. To account for an anticipated 20% dropout rate, the sample size was increased to 44 participants per group, yielding a total of 88 participants.

Approximately 200 pregnant women attending routine antenatal care (ANC) visits at the community health centers were sequentially approached and invited to participate in the study. They were first interviewed to determine eligibility based on inclusion and exclusion criteria. Those meeting the criteria were provided with detailed information about the study and asked to provide written informed consent. Following consent, a blood sample was collected to assess baseline levels of heavy metals.

Only participants with elevated levels above reference thresholds were considered eligible for inclusion in the intervention phase. For the intervention group, eligible participants were contacted and provided with *M. oleifera* supplements along with instructions for daily consumption over a 2-month period. They were informed that a follow-up blood collection would occur at the end of the supplementation period during a routine visit.

For comparison, the control group was recruited from a different health center in a separate subdistrict administrative unit that did not receive moringa supplementation. This approach minimized contamination between groups and allowed for feasible implementation of the intervention. Follow-up blood sampling was also conducted after 2 months, aligned with their next scheduled antenatal visit, but without providing moringa supplementation.

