### Expected Outcomes

#### Reduction in Blood Heavy Metal Levels

The primary outcome of this study is the reduction in blood Pb/Cd/Hg level. The hypothesis is that supplementation with *M. oleifera* will result in a reduction in the blood levels of heavy metals in pregnant women compared to those in the control group. Hence, the expected results are as follows: (1) A measurable decrease in the blood Pb/Cd/Hg concentration will be observed in the group receiving *M. oleifera* supplementation for 2 months. (2) The intervention group is expected to show a greater reduction in blood heavy metal levels than the control group, based on pre- and post-test analyses.

Scientific implications expected are that the result would provide evidence that *M. oleifera* has the potential to detoxify, thereby demonstrating that it is a safe and effective approach to reducing heavy metal accumulation in expectant mothers, who are at a higher risk of exposure to environmental pollutants.

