#### Safety and Tolerability of *M. oleifera*

Hypothesis: *M. oleifera* supplementation will be safe for pregnant women, with no significant adverse effects reported during the intervention period. Hence, the expected results are as follows: (1) Minimal to no adverse effects in the group receiving *M. oleifera* supplementation. (2) This safety profile is consistent with previous studies indicating that 2000 mg/day is safe for pregnant women.

This will provide further evidence that *M. oleifera* is a safe supplement for pregnant women, supporting its use in future clinical applications and maternal health programs.

In the final analysis, changes in heavy metal levels (Pb, Cd, and Hg) will be reported individually, as well as in aggregate if appropriate. Similarly, biomarkers of oxidative stress (8-OHdG and MDA) will be analyzed and reported separately. While the study is not powered for definitive subgroup comparisons, exploratory reporting by relevant characteristics (eg, trimester, nutritional status, and baseline exposure level) will be presented to generate hypotheses for future studies.

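### Three jointly primary metals, each tested one-tailed at .05, with no rule for how many must succeed and no deciding analysis named

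*Protocol article*

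**What the plan says.** - **Primary outcome.** Expected Outcomes states: "The primary outcome of this study is the reduction in blood Pb/Cd/Hg level". The abstract uses the plural: "Primary outcomes will include changes in heavy metal concentrations". No metal is ranked above the others.
- **Error level.** Data Analysis states: "The significance level (alpha) will be set at .05, and all tests will be one-tailed". The sample size in Participant Recruitment uses the same level undivided: "Using a 1-sided test with *α*=.05 and 80% power, the minimum required sample size is 37 participants per group".
- **Composite.** Data Analysis adds: "Reduction in each individual heavy metal will be reported separately, along with a composite index". Expected Outcomes says changes in the metals "will be reported individually, as well as in aggregate if appropriate". The index is not defined and is not called primary.
- **Methods.** Data Analysis lists paired t or Wilcoxon signed-rank tests within each group, DiD between groups, and ANCOVA to adjust for baseline differences. All analyses are run with and without outliers. No order of precedence is given.
- **Hypothesis.** The Introduction compares women with their own levels before supplementation. Expected Outcomes compares them with the control group.
- **Interaction.** Treatment-by-baseline terms are added to the ANCOVA, followed by: "If no significant interaction is found, primary analyses will focus on aggregate outcomes across all participants".

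**The concern.** A per-test level of .05 bounds the error of a study claim only if one test decides the claim, or if a rule says how several combine. Here three outcomes share primary status, and a reader cannot tell whether a fall in one metal alone would confirm the hypothesis. One-sided .05 also allows twice the favourable-direction error of a two-sided .05 test.

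Leaving the methods unranked adds freedom that cannot be quantified from the article. The paired comparison is the weakest route. Women were selected for metal levels above a reference value, so some fall at follow-up is expected from regression to the mean alone, in the direction that a one-tailed test rewards.

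At stake is a claim of detoxification in pregnancy resting on one metal out of three, or on a before-after change. The Dissemination Plan intends the results to feed into maternal health programs.

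**Working it through.** **1. The article's own figure.** Inputs from Participant Recruitment: d = 12.96/30.68 = 0.42, one-sided alpha .05, power 80%, stated n = 37 per group.
- Two-group comparison: n = 2 × ((1.645 + 0.842)/0.42)² = 70.1, so 71 per group. The exact t calculation also gives 71.
- One-sample or paired t test: n = 37 exactly.

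So 37 is reproduced only as a paired calculation, although the text describes a difference between treatment groups. For this point it shows two things: the full one-sided .05 was used without splitting, and the unclear choice between a paired and a between-group contrast reaches the sample size too.

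**2. Chance of at least one false positive under no effect, if any one metal suffices.** Inputs: three tests at one-sided .05. For independent metals this is 1 − 0.95³ = 0.143. The article gives no correlation between the metals' test statistics, so a common value from 0 to 0.9 is assumed (simulation, 2,000,000 draws). The last column adds an equal-weight composite, which is also an assumption because the index is undefined.

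| Correlation | Any of 3 metals | Ratio to .05 | Any of 3 or composite |
|---|---|---|---|
| 0 | 14.3% | 2.9 | 15.5% |
| 0.3 | 13.0% | 2.6 | 13.5% |
| 0.5 | 11.8% | 2.4 | 12.1% |
| 0.7 | 10.3% | 2.1 | 10.3% |
| 0.9 | 8.0% | 1.6 | 8.0% |

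The composite is built from the three metals, so it adds at most 15.5 − 14.3 = 1.2 points.

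**3. How much depends on the missing rule.** If all three metals had to succeed, the figure for independent metals would be 0.05³ = 0.0001, far below 5%. The same text therefore allows anything from almost no error to about 14%.

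**4. Effect of sidedness.** Three independent tests at .025 in the favourable direction give 1 − 0.975³ = 7.3%, about half of 14.3%.

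**5. Normality step.** In a simulation with no effect (26 per arm, lognormal data, 6,000 trials), following the check as a fixed rule left the error for one metal at 5.0%. Free choice of the best of three tests gave 7.9%.

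**6. Power cost of control.** Two-group t test, d = 0.42, noncentrality 0.42 × √(n/2), favourable direction. Holm's first two-sided step is .05/3 = .0167, or .0083 in one tail.

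| n per group | Noncentrality | One-sided .05 | Two-sided .05 (one named metal) | Two-sided .0167 |
|---|---|---|---|---|
| 26 | 1.514 | 44% (critical t 1.676) | 32% (2.009) | 18% (2.477) |
| 44 | 1.970 | 62% (1.663) | 50% (1.988) | 32% (2.442) |

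**The case against.** **Status of the findings.** The Discussion calls the results preliminary, exploratory and hypothesis-generating, and multiplicity detail may sit in an analysis plan that is not shown. This softens the point but does not remove it. The article itself fixes the level and tail of every test, names a three-metal primary outcome and states a primary hypothesis. Expected Outcomes anticipates showing a safe and effective approach.

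**Stronger readings that a reader might infer, and that the text does not support:**
- *The composite is a fourth primary outcome, giving 18.5%.* Nothing calls it primary. The figure 1 − 0.95⁴ treats as independent an index computed from the other three.
- *The error is three times a promised 5%.* The .05 is a per-test level, and no familywise level is stated. A ratio near three needs independent metals and an any-one-metal rule.
- *The normality step lets the analyst pick a method.* It is an ordered rule: check, transform (log is the example given), then "If normality cannot be achieved, nonparametric tests". Followed as a rule, it did not raise the error.
- *The nonparametric fallback discards covariate adjustment.* ANCOVA is stated without condition, and nothing says that Mann-Whitney replaces it. The text merely leaves this unsaid.
- *The interaction result switches the primary endpoint.* The sentence follows the subgroup text and can simply mean the whole sample rather than subgroups. It is ambiguous and no more.
- *A rise in metals would be hidden.* Changes in each metal are to be reported individually. A one-tailed test only withholds a significance statement about a rise.

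**Conclusion.** The point holds in this form: three metals share primary status, each is tested one-tailed at .05, and the article states neither a success rule nor multiplicity control. Paired tests, DiD and ANCOVA are unranked. The one-tailed rule also takes in interaction tests without a predicted direction.

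If one significant metal is enough, the false-claim chance is roughly 8% to 14% (12% at correlation 0.5), and an equal-weight composite adds about one point at most. This rests on two assumptions, the any-one-metal rule and the range of correlations. The extra error from choosing among unranked methods is not quantified. The change should be made before the results are analysed, but the article's own caution about its findings keeps this short of a fatal flaw.

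**What to change.** 1. Name one primary analysis: ANCOVA of log follow-up concentration on log baseline, arm and the listed covariates, for each metal, with two-sided 95% intervals.
2. Apply Holm across lead, cadmium and mercury, or name one metal as primary and make the other two secondary.
3. Label the composite, DiD, outlier-excluded and paired results supportive. Note that the paired results carry regression to the mean.
4. Test interactions two-sided, and state that the primary analysis uses the whole sample whatever the interaction shows.
5. State that any nonparametric fallback for the group comparison keeps the covariates.

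Choosing ANCOVA over DiD is a judgement in a nonrandomized design. What matters most is that one is named and the other is shown alongside.

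**Cost.** The wording is simple, but the power loss is not small. At d = 0.42, Holm's first two-sided step leaves 18% power instead of 44% at 26 per group, and 32% instead of 62% at 44 per group. One named metal tested two-sided at .05 loses less (32% and 50%). The sample size statement assumes an undivided one-sided .05, so it must be revised to match. These figures are for an unadjusted t test.

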### Intervention Group

In addition to receiving iron capsules, which are standard supplements provided by the health centers as part of the national prenatal care program, participants in the intervention group also received *M. oleifera* extract supplementation at a dose of 2000 mg/day, administered as 2 capsules taken twice daily (totaling 2000 mg/day) for a continuous period of 8 weeks. Supplementation began immediately upon enrollment, which occurred between gestational weeks 20 and 32. Therefore, the regimen lasted from the time of enrollment until 8 weeks later, typically ending between weeks 28 and 40 of gestation. For participants enrolled in the late third trimester who delivered before completing the full 8 weeks, they were instructed to continue consuming the remaining *M. oleifera* supplements until the full course was completed. This approach aimed to ensure consistency in the intervention dosage, regardless of the timing of delivery, and to maintain the study’s internal validity.

To support adherence, we collaborated with health cadres at each participating health center. The cadres will be responsible for supervising, reminding, and ensuring that the mothers consistently take the moringa capsules. A WhatsApp group was established specifically for the cadres to facilitate regular communication, provide reminders, and monitor the supervision process throughout the 8-week supplementation period. We have also added a simple adherence log that will be maintained by the cadres, documenting capsule intake daily based on direct questioning or observation. These dual approaches—cadre monitoring and pill counts—will allow us to triangulate adherence data and better distinguish true intervention effects from variability due to compliance.

Participants will be actively monitored for adverse events throughout the 8-week intervention period. At the follow-up visit, participants will be asked about any symptoms or side effects experienced, using a structured checklist and open-ended questions. Specific adverse events of interest include gastrointestinal discomfort (nausea, vomiting, and diarrhea), allergic reactions (skin rash and swelling), and general intolerance to the supplement.

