## Results

Overview

The study was funded in 2024 and data collection began in July 2024. A total of 26 mothers in each group have participated. As of February 2025, the laboratory analysis is ongoing for the second step. We expect the results to be published at the end of 2025.

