#### Reduction in 8-OHdG and MDA Concentrations

Hypothesis: *M. oleifera* will reduce 8-OHdG and MDA levels in pregnant women compared with the control group.

The expected results are as follows: (1) Significant reduction in 8-OHdG and MDA levels in the intervention group, indicating a protective effect against oxidative stress and DNA damage. (2) The intervention group will show lower levels of 8-OHdG and MDA after the intervention than the control group.

These findings will indicate that the antioxidant compounds of *M. oleifera* are effective in inhibiting DNA damage and protecting cells against oxidative stress. This is especially important for pregnant women to ensure fetal health and reduce complications.

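### Every test is one-tailed towards reduction, so a rise relative to control in a metal or oxidative marker can never be significant, and the plan gives no reading for one

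*Protocol article*

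**What the plan says.** The Data Analysis section fixes the level and direction of testing for the whole study: "The significance level (alpha) will be set at .05, and all tests will be one-tailed". It does not name the tail, but the hypotheses do. The Introduction expects lower values after supplementation than before. Under Expected Outcomes, supplementation "will result in a reduction in the blood levels of heavy metals in pregnant women compared to those in the control group", and for the oxidative markers it "will reduce 8-OHdG and MDA levels in pregnant women compared with the control group". The between-group analysis is difference-in-differences, "to measure the difference in changes between the intervention and control groups", with ANCOVA adjustment, and no exception to one-tailed testing is made for it.

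The planned output is worded in the same direction: "Reduction in each individual heavy metal will be reported separately, along with a composite index". The closing text of Expected Outcomes is neutral: "changes in heavy metal levels (Pb, Cd, and Hg) will be reported individually, as well as in aggregate if appropriate", and 8-OHdG and MDA are reported separately.

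The Discussion (Principal Anticipated Findings) takes up two cases: positive outcomes, and the absence of significant effects. For the second it offers dose, duration, sample size and individual variability among the possible reasons. On safety, the Intervention Group section says: "Specific adverse events of interest include gastrointestinal discomfort (nausea, vomiting, and diarrhea), allergic reactions (skin rash and swelling), and general intolerance". It adds pregnancy complications and hospitalizations as serious events. On enrolment, the Results state: "A total of 26 mothers in each group have participated".

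**The concern.** A one-tailed test suits a question in which the other direction does not matter. Here it does. The women are enrolled because mercury, lead or cadmium exceeds a reference value, and the Introduction describes prenatal exposure as particularly harmful. The article also says that human evidence on moringa and metal levels is limited, so a movement in the wrong direction cannot be excluded beforehand. The groups come from different health centres with different pollution sources, and that could also produce a relative rise.

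If a marker rose relative to control, the stated rule would return a p value close to 1. The result would then sit most naturally with the Discussion's case of no significant effects, whose listed reasons do not include worsening. The safety monitoring would not pick it up either, because it covers symptoms and clinical complications. A possible harm signal would be on record as a signed number, with no rule saying how to read it.

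**Working it through.** **The plan's own figure.** The Participant Recruitment section takes a mean difference of 12.96 ng/mL and a pooled SD of 30.68 ng/mL, so d = 12.96/30.68 = 0.42. With one-sided alpha .05 and 80% power it states 37 per group. A one-sided paired (one-sample) t test at d = 0.42 gives 36.44, rounded up to 37; the two-sided version gives 46.45, rounded up to 47. The sample size is therefore one-sided, in agreement with the Data Analysis section. (A two-group one-sided t test needs 71 per group; that is a separate matter.)

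**The logical step.** A test that rejects only for a negative difference needs an estimate below zero. An observed rise relative to control therefore cannot be significant, whatever its size and whatever n is.

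This concerns the difference from control only. Suppose both groups rise, by 0.2 SD with moringa and 0.7 SD in control, at 26 per group. The difference is −0.5 SD, t = −0.5/0.277 = −1.80, and the one-tailed p is 0.039 in favour of moringa.

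**Size of the gap.** Work in SD units of the analysed quantity (for difference-in-differences, the change), unadjusted, with women independent. SE = √(2/n) and df = 2n − 2.

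At n = 26, SE = √(2/26) = 0.277 and df = 50. For an observed rise of 0.8 SD (an illustrative value):
- t = 0.8/0.277 = 2.88
- one-tailed p for reduction = 0.997
- two-sided p = 0.006
- 95% interval = 0.8 ± 2.009 × 0.277 = 0.24 to 1.36

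**What a two-sided 95% interval could flag.** The smallest observed rise whose interval lies above zero is the half-width, t(0.975) × SE. At n = 26 this is 2.009 × 0.277 = 0.56 SD.

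Allocation was by centre, three per arm. For a rough clustering check, multiply SE by √(1 + (m − 1)ICC) with m = 26/3 = 8.67, and use 4 df (t = 2.776). The document gives no ICC; 0.01 to 0.05 is an assumption.
- ICC 0.01: SE = 0.277 × √1.077 = 0.288, half-width 0.80 SD
- ICC 0.05: SE = 0.277 × √1.383 = 0.326, half-width 0.91 SD

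The 0.8 SD example therefore sits on the margin once clustering is allowed for: the interval is 0.001 to 1.60 at ICC 0.01 and −0.11 to 1.71 at ICC 0.05.

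**Chance of flagging a true rise of 0.42 SD** (the design effect size, used only as a yardstick; noncentral t):

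| n per group | Independent women | ICC 0.01 | ICC 0.05 |
|---|---|---|---|
| 26 (enrolled) | 32% | 20% | 17% |
| 44 (sample-size text) | 50% | 30% | 22% |
| 59 (recruitment text) | 62% | 36% | 24% |

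**Error rates if the interval is added.** Per marker, 5% in the lower tail plus 2.5% in the upper tail is 7.5% over both directions. Over five independent markers, the chance of at least one false harm flag is 1 − 0.975⁵ = 0.119, about 12%. Carrying the last observation forward is not modelled.

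**The case against.** The strongest reply is that nothing here is wrong on its own terms. The one-tailed choice is prespecified, matches the hypotheses and agrees with the sample-size basis. Interval reporting is commonly left to a full protocol or analysis plan, neither of which is shown. That stands as far as it goes: the absence of confidence intervals from the article is no fault. The point rests on what the article does fix, namely the direction of every test.

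Several stronger readings are tempting, and the documents do not support them.

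- A reader might infer that a rise would be hidden. It would not: signed changes are to be reported for each metal and each oxidative marker.
- A reader might infer that the Discussion commits the authors to calling a rise a lack of effect. It is discussion text with an openly incomplete list of reasons, not a decision rule. It is silent on worsening, and no more than that.
- A reader might infer that one-tailed testing alone would miss a moderate rise. At 26 per group an observed rise of 0.42 SD has a two-sided p of 0.136, so a two-sided test would not call it significant either. Its interval is −0.14 to 0.98 SD with independent women, and reaches reductions of 0.38 to 0.49 SD under the clustering check. Such data would say little in either direction.

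It is also fair to say that the practical consequence is limited. The study calls its findings hypothesis-generating, sensitivity to harm is low, and any flag is confounded with site, as Strengths and Limitations concedes for environmental factors. These facts keep the point minor. They do not remove it, since a possible harm is a hypothesis that the next trial would need to know about.

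**Conclusion.** The point holds and is minor. The stated rule makes a rise relative to control in any of the five markers incapable of reaching significance, in women selected for a high metal level, and neither the Discussion nor the safety text says how to read one. The first part is pure logic and needs no sample-size assumption beyond taking the tail from the hypotheses. The contrast between p values of 0.997 and 0.006 assumes 26 independent women per group and an observed rise of 0.8 SD, without covariate adjustment. With clustering by centre, the two-sided evidence for the same rise weakens to the margin of significance. The article does not suggest that moringa raises these markers, and the efficacy test need not be abandoned.

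**What to change.** Keep the one-tailed .05 test of reduction as the efficacy test. Then add the following.

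1. For each metal and each oxidative marker, report the adjusted between-group difference with a two-sided 95% confidence interval, labelled as a separate harm check.
2. Report an interval wholly above zero as possible harm, with the caution that differences between non-randomised sites may explain it.
3. State that an interval that includes zero is not to be read as absence of harm.
4. State that the interval is not the efficacy criterion. A one-tailed p between .025 and .05 goes with a 95% interval that includes zero; in the case above where both groups rise, p is 0.039 and the interval is −1.06 to 0.06 SD.
5. Add worsening relative to control to the possible readings in the Discussion.

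The cost is some added analysis and wording, with no new data and no change to the sample-size basis. The downsides should be disclosed: the 7.5% total error per marker, the roughly 12% chance of at least one false flag (which site confounding could raise), and the low sensitivity at 26 per group, where only an observed rise above 0.56 SD would be flagged, or above about 0.80 to 0.91 SD with clustering.
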